### Secondary outcome

#### Psychological distress

To evaluate participants’ levels of anxiety and depression symptoms, assessments such as the Hospital Anxiety and Depression Scale (HADS) will be employed. The HADS, developed by Zigmond and Snaith, is a screening tool for non-psychotic anxiety and depression symptoms in hospitalized patients. It includes two anxiety and depression subscales [34]. In this study, we utilized the Malay version of the Hospital Anxiety and Depression Scale (HADS-M), translated by Yahya F. The HADS-M has shown excellent reliability, with a sensitivity of 90.0% and specificity of 86.2% for anxiety and a sensitivity of 93.2% and specificity of 90.8% for depression. These figures indicate that the HADS-M is a highly reliable tool for screening anxiety and depression in the Malaysian population. Additionally, the HADS-M has been validated in a Malaysian hospital setting and has proven to be a valid instrument for assessing psychological distress among patients. The scale’s psychometric properties, including its high sensitivity and specificity, affirm its acceptability and utility in clinical practice within Malaysia [35].

#### Quality of life

Physical condition, social and family situation, emotional state, functional condition, and a breast cancer-specific module make up the five dimensions of Functional Assessment of Cancer Therapy– Breast cancer (FACT-B). The FACT-B consists of 37 items: the higher the score, the better the overall survival treatment and the corresponding dimension [36]. The Malay version of the FACT-B is a reliable and valid tool for assessing the QoL in Malaysian breast cancer survivors. It demonstrated high internal consistency, with a Cronbach’s alpha of 0.88 for the overall scale and values ranging from 0.62 to 0.88 for individual domains. The FACT-B also exhibited strong concurrent validity, as evidenced by significant correlations with the Disabilities of Arms, Shoulders, and Hands (DASH) questionnaire and the Patient Health Questionnaire-Anxiety Depression Scale (PHQ-ADS). Additionally, the tool detected differences in physical, functional, and QoL measures between participants with and without lymphedema, confirming its known-group validity. These strong psychometric properties highlight the FACT-B’s suitability for use in clinical and research settings to evaluate the impact of breast cancer and its treatment on patients’ well-being in Malaysia [37].

#### Psychological inflexibility

The AAQ-II assessed psychological inflexibility or experiential avoidance. There are seven items in AAQ-II. A higher AAQ-II score suggests more psychological inflexibility [38]. The Malay version of the AAQ-II has demonstrated strong psychometric properties, making it a reliable and acceptable tool for assessing psychological inflexibility among Malay-speaking populations. It exhibited good content validity, reflecting the relevance and representativeness of its items. The internal consistency was high, with a Cronbach’s alpha value of 0.91, and the tool also showed excellent parallel reliability. Exploratory factor analysis confirmed that the AAQ-II Malay version is a unidimensional instrument. Adequate concurrent validity was established through significant correlations with other measures of similar constructs. Additionally, the sensitivity and specificity analyses indicated that the AAQ-II Malay version effectively distinguishes cancer patients with significant psychological inflexibility (scores above 17.5) from those without. These findings support the AAQ-II Malay version’s use in clinical and research settings to measure psychological inflexibility accurately [39].

#### Social support

The Malay version of the Multidimensional Scale of Perceived Social Support (MSPSS-M) for cancer patients covers three dimensions of social support (Family, Friends, and Significant Others). The MSPSS-M consists of 12 items, with higher scores indicating greater perceived social support by the patient. The MSPSS-M has demonstrated strong psychometric properties, making it a reliable and valid tool for assessing perceived social support among cancer patients in Malaysia. The MSPSS-M exhibited high internal consistency, with Cronbach’s alpha values ranging from 0.900 to 0.932, indicating excellent reliability. Confirmatory factor analysis supported the three-factor model of the original English version, confirming the construct validity of the MSPSS-M. Additionally, the MSPSS-M showed good convergent and discriminant validity, ensuring it accurately measures perceived social support and distinguishes it from unrelated constructs. The tool also demonstrated good content and face validity, indicating that the items are appropriate, comprehensive, and understandable for the target population. The MSPSS-M is a reliable and acceptable instrument for clinical and research settings to assess perceived social support among Malay-speaking cancer patients in Malaysia [40].

## Statistical analysis

### Descriptive analysis

Statistical software for social sciences (SPSS version 27) will be used to conduct data analysis. The study of sociodemographic data will make use of descriptive statistics. Race, age, marital status, educational background, work position, and illness state, including the stage at diagnosis, chemotherapy regimen, and time since diagnosis, are all described using frequency and percentage. Before implementing the ACT intervention, inference analysis will examine the significant differences between the waiting and intervention groups. The study’s primary analysis will adhere to the intention-to-treat (ITT) principle. Furthermore, the main effect will be accompanied by a 95% confidence interval. Statistical significance will be determined using a two-tailed approach and set at p<0.05.

To address any instances of missing data, the approach will be as follows: If missing data accounts for less than 5% of the total collected data, they will be disregarded. In cases where missing data exceed 5% but fall below 40% of the total collected data and are assumed to occur randomly, multiple imputations using restricted maximum likelihood estimation will be conducted using Stata 15. However, if missing data surpass 40% of the total collected data or are presumed to be non-random or entirely random, only the available data will be utilized for analysis in the study, and any absence of data will be acknowledged as a limitation in subsequent publications of the study’s findings [41].

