### Mixed ANOVA analysis

The comparison of mean differences before and post-intervention will be examined to see whether any changes in illness cognition, anxiety, depression, psychological inflexibility, QoL, and social support among breast cancer patients in response to ACT intervention. Then, while controlling for confounders, mixed ANCOVA will be used to look at any significant changes in the measured variables between the waiting and intervention groups, with the group as the between-group factor and time as the within-group factor. A few confounding factors that may affect disease acceptance in cancer will be taken into account and controlled by using mixed ANCOVA, such as the level of pain and fatigue and monthly income [42, 43]. Age is also included as a covariance.

The effect sizes will be determined to evaluate how much patients’ perceptions of the measured variables changed with and without an ACT intervention. The formula of Cohen’s d (Rosnow Rosenthal, 1996) [44] is used to calculate the effect size. According to Cohen (1988), the effect size will be considered small if (d = 0.2), medium (d = 0.5), and large (d = 0.8).

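### The missing-data rule can drop randomised patients from an analysis described as intention-to-treat, and may bias the effect when dropout differs by arm

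*Protocol article*

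**What the plan says.** The Descriptive analysis section states that the "primary analysis will adhere to the intention-to-treat (ITT) principle". It then sets three branches for missing data:

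- Small amounts: "If missing data accounts for less than 5% of the total collected data, they will be disregarded". The mechanism plays no part here.
- Intermediate amounts: data that "exceed 5% but fall below 40% of the total collected data and are assumed to occur randomly, multiple imputations using restricted maximum likelihood estimation".
- Everything else: if more than 40% is missing, or if the gaps "or are presumed to be non-random or entirely random, only the available data will be utilized for analysis". The only stated consequence is that "any absence of data will be acknowledged as a limitation in subsequent publications".

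The Mixed ANOVA analysis section names the main model, a mixed ANCOVA "with the group as the between-group factor and time as the within-group factor", with pain, fatigue, monthly income and age as covariates.

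The Procedure section gives three assessments. The objectives list T0 to T3, which is four. The sample-size paragraph under Participants allows for 20% dropout.

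**The concern.** Three features of the rule combine badly.

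1. The thresholds refer to all data collected. They do not look at the disease-acceptance score, at a given visit, or at either arm separately. A sizeable loss of the primary outcome at one visit is diluted by complete data from the other visits.
2. Ignoring those gaps is not neutral. A standard repeated-measures procedure with time as the within factor keeps only patients with every visit. A patient who misses the final visit therefore leaves the analysis entirely, together with an observed T1 score.
3. Missingness presumed non-random is the case in which analysing available cases is hardest to defend, and it is the case given that analysis.

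At stake is whether the primary comparison covers the patients who were randomised, and whether its estimate can be trusted if one arm loses more of its poorly adjusting patients.

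**Working it through.** **Figure in the plan.** The missing-data rule contains no computed result. The related figure is the 20% dropout allowance. An ANCOVA F test with 0.46 read as Cohen's f, three covariates, alpha 0.05 and power 0.95 needs 64 patients, and 64 / 0.80 = 80. The stated 80 is reproduced, and nothing below changes it.

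**What the 5% threshold lets through.** With V visits, if a fraction p of patients misses only the final visit, the missing share of all scores is p / V. The gap is ignored when p < 0.05 × V.

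- V = 3: p < 0.15. Of 80 patients, 11 missing gives 11 / 240 = 4.6%, which is ignored.
- V = 4: p < 0.20. Of 80 patients, 15 missing gives 15 / 320 = 4.7%, which is ignored.

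**Where the planned 20% dropout falls.**

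- Three visits, lost at the final visit only: 0.20 / 3 = 6.7%.
- Three visits, lost at both post-baseline visits: 0.20 × 2 / 3 = 13.3%.
- Four visits, lost at the final visit only: 0.20 / 4 = 5.0%, on the boundary.
- Four visits, lost after baseline: 0.20 × 3 / 4 = 15%.

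The 6.7%, 13.3% and 15% cases go to multiple imputation if assumed random, and to available data only if presumed non-random or entirely random.

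**What complete-case analysis does to the estimate.** The documents give no dropout pattern, so these inputs are assumptions:

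- three visits, all pairwise correlations 0.5, true effect 0.50 SD at both post-baseline visits;
- final-visit loss of 20% in control and 8% in ACT, an average of 14%, so 0.14 / 3 = 4.7% of the data and ignored under the rule;
- logistic dropout, more likely with a poor score, slopes 0.5, 1.0 and 1.5;
- at least 400,000 simulated patients per arm, so simulation error is negligible.

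Results for T1 when dropout depends on the observed T1 score, from the weakest to the strongest slope:

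| Complete-case contrast | Estimate (true 0.50) | Bias |
|---|---|---|
| Change from baseline | 0.471 to 0.436 | about -6% to -13% |
| Baseline-adjusted | 0.456 to 0.402 | about -9% to -20% |

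The final-visit estimates are almost the same when dropout depends on the unseen final score. Using every observed T1 score with baseline adjustment returns 0.50.

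**When the bias disappears.** With 14% loss in both arms and the same slopes, every complete-case estimate stays within about 0.495 to 0.506, whether dropout depends on the seen or the unseen score. Completely random loss also gives about 0.50.

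**When the sign reverses.** A second simulation used 40 per arm, 14.5% final-visit loss, slope 1.5, and dropout running in opposite directions in the two arms. The available-case final-visit estimate was 0.59 when dropout depended on the T1 score and 0.76 when it depended on the unseen final score. Imputation from the earlier visits gave 0.50 and 0.73. It repairs the first case and hardly touches the second.

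**The case against.** The strongest reply is that the rule does less harm than it seems.

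- **The planned dropout would mostly be imputed.** Over three visits, a 20% loss exceeds 5% and goes to multiple imputation if assumed random. This stands. A reader might infer that the rule prevents any correction, and the text does not support that. It remains true that loss just under 15% is ignored, that over four visits the planned 20% at the final visit sits on the boundary, and that presumed non-random loss is never imputed.
- **Bias is not a given.** The 20% versus 8% imbalance is an assumption. Both arms get equal sessions and time from the same therapists, so strong imbalance is not the obvious expectation. Branch three also covers entirely random loss, where available cases are unbiased. This stands, so one cannot say that the rule biases the effect, only that it may.
- **Raw post-scores give a larger figure.** A complete-case difference in raw scores is about 0.37 to 0.45 SD under the same assumptions, up to about a quarter too low. The plan analyses change over time with covariates, so that figure overstates the matter.
- **Available data can be compatible with intention-to-treat.** This is true in a likelihood-based mixed model that keeps every patient with any score. The article names a mixed ANCOVA and no procedure, so listwise deletion is inferred from the usual implementation. A flat contradiction is too strong: the plan does not ensure the analysis it promises.
- **Other faults a reader might add.** The phrase "multiple imputations using restricted maximum likelihood estimation will be conducted using Stata 15" reads oddly, but REML may be meant as the estimator for the model fitted afterwards, and no effect on the result has been shown. The choice of branch does depend on the observed amount and presumed type of missingness. However, the rule is written in advance, does not depend on treatment results, and the Blinding section has uninvolved statisticians analyse before final unblinding.
- **A statistical analysis plan may exist.** The absence of sensitivity analyses from the article is therefore no fault by itself. The rule, however, is stated in full, and an analysis plan could only overrule it.

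**Conclusion.** The concern holds in a conditional form. As written, the rule can exclude randomised patients from an analysis described as intention-to-treat, and it may bias the effect. The threshold arithmetic follows directly from the text: final-visit loss of just under 15% of patients over three visits, or just under 20% over four, is ignored. Exclusion of those patients rests on one assumption, that the mixed ANCOVA is run as a standard repeated-measures procedure. The assignment of presumed non-random missingness to available data only is explicit.

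The size of any bias is illustrative. Under the assumed 20% and 8% outcome-dependent loss, an effect of 0.50 SD is estimated at about 0.44 to 0.47 SD on change from baseline, or 0.40 to 0.46 SD baseline-adjusted. Other patterns can inflate it. There is essentially no bias if loss and mechanism are the same in both arms or if loss is completely random. The documents do not show which pattern will occur, so neither the presence nor the direction of bias can be asserted.

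**What to change.** - Delete the 5% and 40% thresholds and the branch that falls back to available data.
- At any level of missingness, fit a REML linear mixed model to all observed post-baseline acceptance scores of all randomised patients, with group, visit, group-by-visit, baseline acceptance score and the planned covariates (pain, fatigue, monthly income, age). Patients with no post-baseline score add nothing to this model and enter through the imputation analyses below.
- Report missingness of the primary outcome by arm and visit.
- Where non-random dropout is suspected, run multiple-imputation sensitivity analyses in which the imputed scores of dropouts are shifted by a range of deltas. Neither the mixed model nor imputation under missing-at-random cures non-random loss.

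Which visit carries the primary contrast is a separate decision for the sponsor and is not settled by this change.

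The cost is revised wording and a little more analysis work in SPSS or Stata, both already named. Data collection and the sample size are unchanged. The change should be made before outcome data are seen, because a later change could look data-driven.

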### Mixed ANOVA analysis

The comparison of mean differences before and post-intervention will be examined to see whether any changes in illness cognition, anxiety, depression, psychological inflexibility, QoL, and social support among breast cancer patients in response to ACT intervention. Then, while controlling for confounders, mixed ANCOVA will be used to look at any significant changes in the measured variables between the waiting and intervention groups, with the group as the between-group factor and time as the within-group factor. A few confounding factors that may affect disease acceptance in cancer will be taken into account and controlled by using mixed ANCOVA, such as the level of pain and fatigue and monthly income [42, 43]. Age is also included as a covariance.

The effect sizes will be determined to evaluate how much patients’ perceptions of the measured variables changed with and without an ACT intervention. The formula of Cohen’s d (Rosnow Rosenthal, 1996) [44] is used to calculate the effect size. According to Cohen (1988), the effect size will be considered small if (d = 0.2), medium (d = 0.5), and large (d = 0.8).

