### Randomization and allocation concealment

Permuted block randomization with an allocation ratio of 1:1 is carried out. Participants will be randomly assigned based on odd (Group A) and even (Group B) rows using a computer-generated randomisation sequence. The randomization sequence, informing participant assignment to either intervention (Group A) or waitlist control (Group B) condition, is provided in opaque envelopes by one investigator not involved in participant recruitment or assessment. Blinded to the study assignment, participants will be allotted to either group in a 1:1 ratio. Participants will be randomly assigned to two groups: the intervention group receiving ACT intervention or the control group receiving standard treatment with non-therapeutic intervention.

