### Participants

Patients receiving treatment in oncology clinics at Universiti Sains Malaysia and Hospital Seberang Jaya will be recruited for the study. The criteria for study participation include: (1) diagnosed with breast cancer, (2) aged 18 years or older, (3) currently receiving treatment, (4) able to understand and communicate in the study language, and (5) willing to participate in the intervention and follow-up assessments. Patients are deemed ineligible for the study if they: (1) have severe cognitive impairment or significant psychiatric comorbidities (e.g., psychosis, substance abuse) that could hinder their participation in the study, (2) are diagnosed with malignant tumors, and (3) currently receiving any other form of psychological therapy intervention.

Sample size calculations will be based on power analysis using established effect sizes from previous studies on ACT interventions and disease acceptance among similar populations. We conducted an a priori power analysis using GPower 3.1.9.7 to calculate the estimated sample size needed for mixed ANOVA with control of three covariates: the type I error was 0.05, with a power of 0.95, three covariates, with two intervention groups and an effect size of 0.46 by referring to an RCT on the efficacy of ACT on illness cognition among breast cancer patients [28], Hence, the estimated sample size needed is 80 (with the inclusion of a 20% dropout rate). Hence, 40 subjects are required per group.

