### Procedure

This research used a consecutive sampling technique for subject recruitment before randomly assigning them to the intervention and control groups. Potential participants will first be screened to determine their eligibility for study participation. Invitations to take part in this trial will follow. The investigator will ensure that participants receive a thorough explanation of the study goals and methods before agreeing to join the study. Participants will sign the Subject Information and Consent Form and Participant’s Material Publication Consent Form before enrolling in the research to indicate their agreement. We will ensure the participants’ anonymity and inform them about their right to withdraw from the study at any point, guaranteeing their confidentiality and autonomy. To ensure participants receive similar intervention, the trial adapts a brief ACT module by Shari et al. [31]. The therapist will administer the intervention when patients are in the hospital for treatment. The assessment batteries will be issued at three specific time points: before the intervention, immediately after the intervention, and three months following the intervention.

Participants in the control group will receive the non-therapeutic approaches, such as reassurance, to allow patients to ventilate their problems and to conduct relaxation techniques such as deep breathing. The intervention and the control groups will receive a 4-session program to ensure ethical considerations and participant access to the intervention. The enrolment, interventions, and assessments of the study are summarized in Fig 1. Fig 2 shows the flow of the research procedures and outcome measures.

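### The primary mixed ANCOVA uses the baseline score as a level of time, not as a covariate, and leaves the decisive term unnamed; baseline adjustment would gain precision at almost no cost

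*Protocol article*

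**What the plan says.** The Mixed ANOVA analysis section fits a mixed ANCOVA "with the group as the between-group factor and time as the within-group factor". It describes the aim as finding changes between the groups, after a comparison of means before and after the intervention. The confounders to be controlled are introduced by "such as the level of pain and fatigue and monthly income", and age is added. The baseline value of the outcome is not named.

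Baseline belongs to the time factor. The Procedure section schedules assessments at "three specific time points: before the intervention, immediately after the intervention, and three months following the intervention", and the primary and secondary objectives list T0 among the time points compared. The objectives announce three time points but list four (T0 to T3), so the number of levels is itself unsettled.

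The Descriptive analysis section promises a 95% confidence interval for the main effect without defining that effect. It adds: "Statistical significance will be determined using a two-tailed approach and set at p<0.05". The sample size in the Participants section is the number "needed for mixed ANOVA with control of three covariates", with these inputs: "the type I error was 0.05, with a power of 0.95, three covariates, with two intervention groups and an effect size of 0.46". The metric of 0.46 is not stated. The result is 80 in total, including 20% dropout.

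**The concern.** The baseline score is usually the strongest single predictor of the later score, and this trial collects it in any case. As a level of the time factor it does one of two things, depending on which term is tested.

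- **Group main effect.** The baseline difference, which is zero in expectation under randomisation, is averaged into the treatment difference.
- **Group-by-time.** Baseline is subtracted, as in a change-score analysis, rather than adjusted for by regression. Chance imbalance at baseline is then over-corrected whenever the correlation is below 1.

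The article does not say which term decides. An interaction F test with two or three degrees of freedom also does not by itself yield a single treatment difference to carry the promised interval. At stake are the precision of the primary comparison, in a trial whose authors call the sample relatively small, and the clarity of what a significant result would mean.

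**Working it through.** **Inputs from the article:** two-sided alpha 0.05, power 0.95, effect size 0.46, two groups, three covariates, 1:1 allocation, 20% dropout, 80 in total. **Assumptions, because the article gives none:** SD 1, compound symmetry with correlation ρ = 0.3, 0.5 or 0.7, the same effect at every post-baseline visit, complete data on 32 per arm. The covariates other than baseline are ignored in the power comparisons.

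**Step 1: the plan's own figure.** Take a one-degree-of-freedom group effect in an ANCOVA with f = 0.46 and noncentrality λ = N·f². Power is 0.951 at N = 64, and 64/(1 − 0.20) = 80. The stated size is reproduced, with 64 completers or 32 per arm. For two equal groups d = 2f = 0.92. Read as Cohen's d, 0.46 would need about 246 to 248 participants before dropout, so the f reading is the one that fits.

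**Step 2: group main effect over T0 and two later visits.** The expected difference is (0 + d + d)/3 = 2d/3, so 0.92 becomes 0.613. The per-arm variance of the three-visit mean is (1 + 2ρ)/3 = 0.533, 0.667, 0.800. With λ = 16·(2d/3)²/variance = 11.29, 9.03, 7.52 on 1 and 62 df, power is 0.91, 0.84, 0.77. With four assessments the shrinkage is one quarter instead of one third.

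**Step 3: omnibus group-by-time, three assessments.** λ = 64·d²/[6(1 − ρ)] = 12.90, 18.06, 30.09 on 2 and 124 df. Power is 0.90, 0.97, 0.999.

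**Step 4: baseline-adjusted ANCOVA at one visit.** The variance is 1 − ρ² = 0.91, 0.75, 0.51. With λ = 16·d²/(1 − ρ²) = 14.88, 18.06, 26.55 on 1 and 61 df, power is 0.97, 0.99, 0.999.

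**Step 5: the gain from baseline adjustment alone.** At one visit a change score has variance 2(1 − ρ) = 1.40, 1.00, 0.60. The ratio to ANCOVA is 2/(1 + ρ) = 1.54, 1.33, 1.18.

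| d = 0.92, 32 per arm | ρ = 0.3 | ρ = 0.5 | ρ = 0.7 |
|---|---|---|---|
| Group main effect including T0 | 0.91 | 0.84 | 0.77 |
| Omnibus group-by-time | 0.90 | 0.97 | 0.999 |
| ANCOVA at one visit | 0.97 | 0.99 | 0.999 |

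**Step 6: sensitivity to a smaller true effect (d = 0.46, ρ = 0.5).** The main effect has 32% power, group-by-time 45% and single-visit ANCOVA 55%. At this correlation the last two have the same noncentrality (64 × 0.2116/3 = 16 × 0.2116/0.75 = 4.51). The ten points between them therefore come from testing one degree of freedom instead of two, although the ANCOVA uses only one of the two follow-up visits. Like for like, on the mean of both post-baseline visits, a change contrast has variance 0.75 and 55% power; the baseline-adjusted contrast has variance 0.50 and 73%.

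**The case against.** A reader might infer that the model dilutes the treatment effect as such. The article does not support that. Dilution occurs only if the group main effect averaged over T0 decides. The talk of changes, and of means before and after the intervention, reads more naturally as group-by-time, which is undiluted, valid and unbiased under randomisation. Chance imbalance at baseline costs precision; it is not bias.

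A reader might also infer a severe loss by setting the 45% at d = 0.46 against the 73%. That gap mixes baseline adjustment with averaging of visits and with fewer degrees of freedom, and it takes 0.46 as a difference in SDs. At the effect that reproduces the sample size, the interaction keeps 0.90 or more.

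Three further points count for the plan. The promise of an interval for the main effect does not contradict the model, since a mixed ANCOVA can supply a contrast with an interval. The covariate list is introduced as examples and is not closed. A statistical analysis plan is mentioned under Blinding and may name the decisive term.

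All of this limits the size of the point. What remains is that the article itself fixes baseline as a level of the outcome. A score already in the dependent variable would not normally also be a covariate in the same repeated-measures model, so the open list does not supply the adjustment.

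**Conclusion.** The point holds as an inexpensive improvement in precision and clarity, not as an error that invalidates the analysis. Its size depends on the term that decides:

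- **Group main effect:** the loss is material, with power of 0.91 to 0.77 against the planned 0.95 when there are three assessments.
- **Group-by-time:** the loss at the planned effect is at most about 7 points (ρ = 0.3), about 2 at ρ = 0.5 and negligible at ρ = 0.7. It is about 10 points if the true effect is half the planned one and ρ = 0.5.

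For the same contrast at one visit, a change score has 1.18 to 1.54 times the variance of baseline adjustment over the correlations considered. These figures rest on the assumed correlations, compound symmetry, a constant post-baseline effect, 32 completers per arm, and 0.46 read as Cohen's f.

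**What to change.** Make the primary analysis a linear mixed model of the post-baseline scores only. Include group, visit and group-by-visit, the baseline score and baseline-by-visit, and the baseline values of the covariates already named. A constrained-baseline mixed model, with a common baseline mean in both groups, is closely similar and would also serve.

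Name one contrast as decisive: the adjusted group difference, with its 95% CI, either at a pre-named visit or as the average over the post-baseline visits. State that this is the effect for which the interval is promised. The number and timing of the visits must be reconciled between the objectives and the Procedure section before the visit is named. Use the same form for the secondary outcomes.

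The cost is analysis wording and one or two degrees of freedom. No new data are needed, because the baseline score is already collected, and SPSS 27 fits the model. A one-degree-of-freedom adjusted difference also matches the form of test that reproduces the stated sample size.
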